**3.16.6 Diet Practices**

This referred to the total frequency in scores and amount of diet for each food item. Consumption of foods such as fruits, vegetables, seafood, and water were considered as healthy foods while the consumption of foods such as fried foods, fried eggs, fried chicken, fats and oils, plain sugar, sweet snacks, salted fish, and carbonated drinks are considered as unhealthy foods.

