**1.6 Research Hypotheses**

The research hypotheses of this study are:

1. There will be no difference in the socio-demographic characteristics between the intervention and control groups at baseline.

2. The behavioral modification intervention program will be effective in improving the knowledge of CVD and its risk factors, motivation, and behavioral skill score among the participants in the intervention group as compared to control group and also within the groups from baseline to six months among secondary school students in Brong Ahafo, Ghana.

3. The behavioral modification intervention program will be effective in promoting physical activity levels of participants in the intervention group as compared to control group and also within the groups from baseline to six months among secondary school students in Brong Ahafo, Ghana.

4. The behavioral modification intervention program will be effective in reducing the prevalence of smoking among participants in the intervention group as compared to control group and also within the groups from baseline to six months among secondary school students in Brong Ahafo, Ghana.

5. The behavioral modification intervention program will be effective in reducing the prevalence of alcohol consumption of participants in the intervention group as compared to control group and also within the groups from baseline to six months among secondary school students in Brong Ahafo, Ghana.

6. The behavioral modification intervention program will be effective in promoting fruits and vegetable intake among participants in the intervention group as compared to control group and also within the groups from baseline to six months among secondary school students in Brong Ahafo, Ghana.

7. The behavioral modification intervention program will be effective in increasing seafood and water intake and reducing carbohydrates, fats and oils, fried eggs, fried chicken, carbonated drinks, plain sugar, sweet snack, and salted fish intake among participants in the intervention group compared to control group and also within the groups from baseline to six months among secondary school students in Brong Ahafo, Ghana.

8. The behavioral modification intervention program will be effective in reducing body weight and BMI of participants in the intervention group as compared to control group and also within the groups from baseline to six months among secondary school students in Brong Ahafo, Ghana.

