**3.12.2 Questionnaire**

The questionnaire will be pre-tested and assisted self-administered questionnaire in English language as in Appendix. The questionnaire will be divided into ten sections namely, socio demography, dietary intake, smoking, alcohol consumption, physical activity, CVD knowledge, motivation, behavioral skills, BMI (weight and height), and blood pressure (diastolic and systolic). The questionnaires will be administered in a classroom setting in all the selected schools.

Section one of the questionnaire will be used to access students’ age, gender, grade, ethnicity, monthly pocket money, and family history. Data on age will be collected in the form of open ended question and students will fill in the blank space provided. The rest (ethnicity, gender, religion, and family history) are in the form of closed ended questions and students are to choose the answers that will pertained to them.

Section two is a seven-day dietary recall instrument which are foods items mostly consumed in Ghana, the Ghana Demographic and Health Survey, (GDHS), (GSS, 2009; Nti, 2008) to assess dietary consumption. Amounts of each food intake will be stated with the use of handy measure tables (food weights). This are based on the weights of foods with their equivalent handy measure tables which are commonly used

in Ghana (Owusu, Ankrah, Boateng, & Anteh, 1995). Then frequency of consumption of certain foods will be scored based on one (1) for never dietary consumption, two (2) for 2-3 times per week, three (3) for 4-5 times per week, four (4) for 6 times per week, and five (5) for daily intake of a particular food item.

Section three and four are the modified smoking and alcohol questionnaires, Global Youth Tobacco Survey (GYTS) developed by WHO and Centre for Disease Control and Prevention (CDC) (CDC, 2008). It is a school-based adolescents’ self- administered questionnaire which comprised of a set of core questions that will be used to evaluate tobacco and alcohol control and prevention programmes among secondary school students. Students would be classified as never, ever, and current smokers and alcohol consumption. Strict confidentiality will be ensured among researchers to avoid disclosure of smoking and alcohol statuses to school authorities, teachers, or parents.

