**3.15.2 Dependent Variables**

The dependent variables of this study are sub divided into primary and secondary outcomes. There were;

i. The primary outcomes are CVD knowledge and its risk factors, motivation, behavioral skills, physical activity, smoking, alcohol consumption, and dietary intake.

ii. The secondary outcomes are body weight, BMI, diastolic and systolic blood pressures.

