**SDS3**

| Fruit juice | 250 mls pack size | |  | 1 | 2 | 3 | 4 | | 5 |
| --- | --- | --- | --- | --- | --- | --- | --- | --- | --- |
| Malt drink | 330 mls bottle size | |  | 1 | 2 | 3 | 4 | | 5 |
| Minerals | 300 mls bottle size | |  | 1 | 2 | 3 | 4 | | 5 |
| (coke, fanta, |  |  |  |  |  |  |  |  |  |
| sprite, etc) |  |  |  |  |  |  |  |  |  |
| Toffees | 1 average toffee size | |  | 1 | 2 | 3 | 4 | | 5 |
| Sugar (you | Teaspoon size | |  | 1 | 2 | 3 | 4 | | 5 |
| add to food) |  |  |  |  |  |  |  |  |  |
| **25. Snacks** | **Handy measure** | | **Number** | **(1) Never** | **(2) 2-3** | **(3) 4-5** | **(4) 6 Times** | | **(5) Daily** |
|  |  |  | **consumed** |  | **Times** | **Times** | **per week** | |  |
|  |  |  |  |  | **per week** | **per week** |  | |  |
| Biscuit | **1 biscuit** | **(cream** |  | **1** | **2** | **3** | **4** | | **5** |
|  | **crackers size)** |  |  |  |  |  |  |  |  |
| Cakes | Orange size | |  | 1 | 2 | 3 | 4 | | 5 |
| Chips | Empty sardine tin size | |  | 1 | 2 | 3 | 4 | | 5 |
| Doughnuts | Large egg size | |  | 1 | 2 | 3 | 4 | | 5 |
| Fried chicken | Match box size | |  | 1 | 2 | 3 | 4 | | 5 |
| Fried egg | Standard egg size | |  | 1 | 2 | 3 | 4 | | 5 |
| Ice cream | Empty small tomato tin  size | |  | 1 | 2 | 3 | 4 | | 5 |
| Meat/sausage | Empty small tomato tin  size | |  | 1 | 2 | 3 | 4 | | 5 |
| khebab |  |  |  |  |  |  |  |  |  |
| Popcorn | Empty milk tin size | |  | 1 | 2 | 3 | 4 | | 5 |
|  |  |  |  |  |  |  |  |  |  |
| **26. Water** | **Handy measure** | | **Number** | **(1)** | **(2) 1 per** | **(3) 2-3** | **(4)** | **4-5** | **(5) 6 or** |
| **consumption** |  |  | **consumed** | **Rarely** | **day** | **Times** | **Times** | **per** | **more times** |
|  |  |  |  |  |  | **per day** | **day** |  | **per day** |
| Water (daily) | 500 mls (sachet water) | |  | 1 | 2 | 3 | 4 | | 5 |

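### The diet form lists fried egg and fried chicken only under Snacks and does not say where those eaten at meals go, so part of a switch away from frying may go unrecorded for these two foods.

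*Protocol*

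**What the plan says.** Section 3.15.2 of the protocol includes diet among the primary outcomes: "physical activity, smoking, alcohol consumption, and dietary intake". Hypothesis 7 in section 1.6 expects the programme to be effective in "reducing carbohydrates, fats and oils, fried eggs, fried chicken, carbonated drinks, plain sugar, sweet snack, and salted fish intake" relative to control. Section 3.16.6 classes the fried foods as unhealthy ("fried foods, fried eggs, fried chicken, fats and oils, plain sugar, sweet snacks, salted fish, and carbonated drinks are considered as unhealthy foods") and defines the measure item by item: "This referred to the total frequency in scores and amount of diet for each food item". None of these places restricts fried egg or fried chicken to a particular eating occasion.

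The instrument is Section 2 of the questionnaire in Appendix A, a recall of the past seven days. Section 3.12.2 gives the frequency coding: "scored based on one (1) for never dietary consumption, two (2) for 2-3 times per week", then 3 for 4-5 times, 4 for 6 times and 5 for daily.

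- **Item 22, Animal Products,** has a row for eggs and a row for chicken. Neither states how the food was prepared.
- **Item 25, Snacks,** comes after the groups for fats and oils (item 23) and for soft drinks and sweets (item 24). It holds the two fried rows, "Fried chicken | Match box size" and "Fried egg | Standard egg size", beside biscuits, cakes, doughnuts and popcorn.

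The instruction at the head of Section 2 asks for the number of each food consumed and its frequency. It does not say whether the item 22 rows exclude fried forms, or whether the item 25 rows cover meals.

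**The concern.** The quantity named in the hypothesis is all intake of fried egg and fried chicken. The rows that measure it stand under a heading that can be read as an eating occasion. A student who has a fried egg at breakfast meets the general egg row first, where it fits. Three food groups later the student meets the fried row under Snacks, where a breakfast egg may seem not to belong.

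Table 3.1 of the protocol includes eating less fried food in what is taught. Changing from fried to boiled or baked is therefore one of the behaviours that the programme aims at, and the fried rows are the only intake rows that separate fried from non-fried egg and chicken. Item 28 contrasts baked with fried chicken, but it asks for preference rather than intake and does not cover eggs. Once a fried egg has been entered only as an egg, no later analysis can recover how it was cooked.

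**Working it through.** The protocol states no figure for this point, so there is nothing to reproduce. The check sets the outcome definition beside the form and follows one example through the 1-5 coding in section 3.12.2.

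**Step 1: definition against form.** Hypothesis 7 and section 3.16.6 cover fried egg and fried chicken without limit. The form offers a general row (item 22, preparation not stated) and a fried row (item 25, under Snacks), with no rule linking them. Three ways of entering a fried egg eaten at a meal are therefore possible: general row only, fried row only, or both.

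**Step 2: one student.** Assume a student who eats fried egg daily at meals at baseline (code 5 if recorded on a row, code 1 if not) and non-fried egg daily at six months.

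| Where the fried egg is entered at baseline | Eggs row | Fried egg row | Change on fried row |
|---|---|---|---|
| Eggs row only | 5 to 5 | 1 to 1 | 0 |
| Fried row only | 1 to 5 | 5 to 1 | -4 |
| Both rows | 5 to 5 | 5 to 1 | -4 |

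Only the first pattern loses the change. Double entry leaves the fried row intact, and the general egg and chicken rows are not named in hypothesis 7.

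**Step 3: same row choice in both arms (dilution).** Let r be the share of such students who use the fried row for meals, alone or with the general row. The mean recorded change on the fried row is r × (1 - 5) = -4r:

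- r = 1: -4
- r = 0.5: -2
- r = 0: 0

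The protocol gives no value for r, so this is the full possible range for this example and not an estimate.

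**Step 4: row choice that differs by arm (bias).** Suppose nobody's diet changes, every such student eats fried egg daily, and r is the same in both arms at baseline. The mean code at six months is 5r + 1(1 - r) = 1 + 4r. Take 0.80 and 0.60 purely as assumed values:

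- r = 0.80: 1 + 4 × 0.80 = 4.2
- r = 0.60: 1 + 4 × 0.60 = 3.4
- Difference: 4.2 - 3.4 = 0.8 points with identical diets

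If lessons on fried food make intervention students more careful to use the fried row, their arm has the 4.2 and the programme looks worse than it is. If the lessons make them avoid that row, their arm has the 3.4 and it looks better. Nothing in the protocol says which is more likely, or that either occurs.

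**Step 5: reach.** Hypothesis 7 names ten foods: two to increase (seafood, water) and eight to reduce (carbohydrates, fats and oils, fried eggs, fried chicken, carbonated drinks, plain sugar, sweet snack, salted fish). Two of the ten are affected. The sample size calculation in section 3.6 rests on smoking initiation and is not touched.

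**The case against.** The strongest reply is that the form already gives the student the right place. The Section 2 instruction covers the whole diet of the past week, not snacks alone, and there is a row that says fried egg. A student who ate fried eggs at meals and circles never on that row has misreported. The group headings also look like loose groupings rather than eating occasions: the sugar a student adds to food sits under soft drinks and sweets.

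This stands in part. A reader might infer that the form lets students truthfully deny eating fried egg, or that it cannot record fried food eaten at meals. The documents support neither. What remains is a foreseeable misclassification by students who let the heading govern the row.

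The second reply is that the protocol has steps that could find the problem. Section 3.12.2 describes the questionnaire as pre-tested and assisted, section 3.13.2 has 50 students rate order, clarity and appropriateness, and section 3.13.3 adds expert review. These steps may catch the ambiguity, but the protocol gives assistants no rule for resolving it, and the form as printed still contains it.

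Third, reduced frying could also appear in the fats and oils rows (item 23), which hypothesis 7 covers as well. That is true, but it does not repair the two fried items themselves.

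**Conclusion.** The point holds as a minor improvement to the form. The outcome covers all fried egg and fried chicken, the rows that measure it are headed as snacks, and nothing on the form says where the same foods eaten at meals belong. Some loss of the true change on these two rows is possible. It occurs only among students who eat the fried forms at meals and enter them solely in the general rows.

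The size is unknown. The -4r range and the 0.8-point difference rest on assumed shares and show how the mechanism works; they do not measure it. A reader might go further and infer a fixed percentage loss, or a bias in favour of the programme. Neither follows: the protocol gives no shares, the frequency codes are unevenly spaced so a share does not translate simply into a percentage of the true effect, and differential row choice could run in either direction. Randomisation, sample size and the analysis are not affected, and the consequence is confined to two food items within the dietary-intake outcome.

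**What to change.** Before baseline, reword four row labels in Section 2 of the questionnaire:

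- Item 22: *Eggs (not fried)* and *Chicken (not fried)*.
- Item 25: *Fried egg (at a meal or as a snack)* and *Fried chicken (at a meal or as a snack)*.

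Use identical wording at baseline and at six months, in both arms. The form already qualifies other rows in this way, for example white and brown rice, and sugar added to food, so the change fits its style. The cost is a few words on four rows, with no new item, no extra time for students and no change to the analysis.

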**3.16.7 CVD Risk Factor Knowledge**

CVD knowledge are the risk factors and preventive strategies of CVDs. This refers to the total sum of knowledge scores for all items of the CVD knowledge.

**3.16.8 Motivation**

Motivation refers to the total number of questions in the motivation questions that are answered correctly by participants.

**3.16.9 Behavioral Skills**

This refers to the total sum of behavioral skills scores for all items in this section of the questionnaire.

**3.17 Data Analysis**

Data collected will be collated, checked, cleaned, and analyzed using IBM Statistical Package for Social Sciences (SPSS) version 22. The data analysis will be divided into descriptive and inferential statistics. The level of significance for all the statistical tests is set at 0.05. For mean estimations, 95% confidence intervals (CI) will be computed.

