**1.5.2 Specific Objectives**

The specific objectives of this study are:

1. To determine and compare the socio-demographic characteristics among intervention and control groups at baseline.

2. To determine and compare knowledge, motivation, behavioral skills and CVD risk factors (physical inactivity, smoking, alcohol consumption, unhealthy diet, BMI, diastolic and systolic blood pressures) between intervention and control groups at baseline.

3. To develop and implement a behavioral modification intervention program to reduce CVD risk factors among secondary school students in Brong Ahafo, Ghana.

4. To evaluate the effectiveness of behavioral modification intervention program to increase knowledge, motivation and behavioral skill on CVD risk factors between intervention group as compared to control groups at six months post intervention and also within groups from baseline to six months.

5. To evaluate the effectiveness of behavioral modification intervention program to reduce CVD risk factors in intervention group as compared to control group at six months and also within groups from baseline to six months among secondary school students in Brong Ahafo.

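### Seven co-equal primary outcomes (17 endpoints in hypotheses 2-7) are each tested at an unadjusted 0.05 with no success rule, and within-group change is written into every effectiveness hypothesis.

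*Protocol*

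**What the plan says.** Section 3.15.2 of the protocol lists the primary outcomes together, without ranking them: "The primary outcomes are CVD knowledge and its risk factors, motivation, behavioral skills, physical activity, smoking, alcohol consumption, and dietary intake". The abstract and the conceptual framework (section 2.11) list the same seven. Section 3.17 then fixes the threshold: "The level of significance for all the statistical tests is set at 0.05". No hierarchy, adjustment or rule for overall success accompanies it. The sample size in section 3.6 rests on smoking initiation alone, but smoking is not made the deciding outcome.

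Section 1.6 divides the seven outcomes further. Hypothesis 2 covers three scores ("improving the knowledge of CVD and its risk factors, motivation, and behavioral skill score"). Hypotheses 3, 4 and 5 take one outcome each ("promoting physical activity levels of participants"; "reducing the prevalence of smoking among participants"; "reducing the prevalence of alcohol consumption of participants"). Hypothesis 6 covers fruit and vegetables, and hypothesis 7 lists ten further foods and drinks.

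Each of hypotheses 2-9 states effectiveness in two parts, for example "in the intervention group as compared to control group and also within the groups from baseline to six months". Objective 5 in section 1.5.2 does the same ("as compared to control group at six months and also within groups from baseline to six months"), and objective 4 is built in the same way. Section 3.17.3 plans paired t-tests and McNemar tests for the within-group part. The same section assigns the generalized linear mixed model (GLMM), after multiple imputation, to judging the overall effectiveness of the intervention. The abstract says this model tests group, time and their interaction.

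**The concern.** There are two linked problems.

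First, with many primary endpoints each at a full 0.05 and no rule for combining them, the error rate of the trial's overall conclusion is not controlled. A reader of the results could not tell whether one favourable food item among many nulls counts as the programme working.

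Second, a before-after change within an arm is not an effect of the intervention. The primary outcomes come from a self-administered questionnaire, and the same questionnaire is given again at six months. Scores can therefore move through repetition alone, in both arms. Randomisation removes such shared change only in the comparison between arms. Writing the within-group part into the hypotheses leaves open which comparison supports a claim of effectiveness.

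**Working it through.** **Plan's own figure.** The protocol gives no family-wise error rate, so there is none to reproduce. The inputs below are its stated threshold and its own lists.

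**Counting endpoints under the primary outcomes (section 1.6).**
- Hypothesis 2: knowledge, motivation, behavioural skills: 3
- Hypothesis 3: physical activity: 1 (running total 4)
- Hypothesis 4: smoking: 1 (5)
- Hypothesis 5: alcohol: 1 (6)
- Hypothesis 6: fruit and vegetables, counted as one: 1 (7)
- Hypothesis 7: seafood, water, carbohydrates, fats and oils, fried eggs, fried chicken, carbonated drinks, plain sugar, sweet snacks, salted fish: 10 (17)

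Hypotheses 8 and 9 concern secondary outcomes and are left out.

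**Chance of at least one false positive, no true effect, independent tests.** For k two-sided tests at 0.05 this is 1 − 0.95^k. A false claim of benefit uses one tail, 0.025 per test, so the formula becomes 1 − 0.975^k.
- k = 7: 1 − 0.95^7 = 0.302; benefit only, 1 − 0.975^7 = 0.162
- k = 17: 1 − 0.95^17 = 0.582; benefit only, 1 − 0.975^17 = 0.350

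**Effect of correlation.** The protocol gives no correlation between outcomes, so a common value is assumed and varied (simulation, either direction counted):

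| Common correlation (assumed) | 7 outcomes | 17 endpoints |
|---|---|---|
| 0 | 30.2% | 58.2% |
| 0.1 | 29.7% | 56.8% |
| 0.2 | 28.7% | 53.7% |
| 0.3 | 27.2% | 49.5% |
| 0.5 | 23.0% | 38.7% |
| 0.7 | 17.8% | 27.1% |

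At a correlation of 0.7 the rate for seven outcomes is still more than three times 5% (17.8/5 = 3.6).

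**The within-group part.** The joining words can be read two ways. A simulation under no effect and no change over time, with independent endpoints and both directions counted, used the between-group test and the within-intervention test:
- Either result suffices: 8.3% per endpoint; 45% for 7, 77% for 17.
- Both results required: 1.7% per endpoint; 11% for 7, 25% for 17.

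The two readings give very different error rates, and the text does not choose. Neither is a sound test. Under the first, any change over time common to both arms can count as success. Under the second, taken literally for both groups, the control arm, which follows its normal curriculum, must also improve.

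**The case against.** The strongest reply has five parts.

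- **The protocol already names a deciding analysis.** Section 3.17.3 assigns overall effectiveness to the GLMM. This stands, and it makes the fix smaller. It does not say which coefficient decides, on which of the seven outcomes, or that the paired tests are only descriptive.
- **Hypotheses 2-9 are separate claims.** Whether separate claims need family-wise control is debated, and the protocol states no rule that any one success suffices. Both are fair. But the protocol ranks none of the seven, states one general objective of effectiveness, and gives no rule at all for reaching it.
- **Multiplicity procedures often sit in the SAP.** True, but section 3.17 does not leave the matter open. It fixes 0.05 for every test.
- **A reader might infer that a false claim of effectiveness is more likely than not.** The figures do not support this. For the seven declared outcomes the rate is 30%. The 58% needs 17 independent endpoints, no true effect on any, and errors in either direction; it falls below half at a correlation of about 0.3. False claims of benefit reach 16% and 35%. They just pass half (1 − 0.975^28 = 0.51) only if each of the 11 foods is tested on both frequency and amount (6 + 22 = 28 independent tests).
- **A reader might infer that within-group change alone satisfies each hypothesis.** That takes the joining words to mean or. They are ambiguous, and the conjunctive reading makes a false claim harder.

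Other explanations for within-group change should also not be stretched. Regression to the mean is not expected, because students are sampled at random and not selected on extreme outcome values (sections 3.4.2 and 3.5.2). The planned change of measuring staff (section 3.10) affects only anthropometry and blood pressure, which bear on the secondary outcomes. Growth bears mainly on weight and BMI, also secondary. Repeating the questionnaire is the mechanism that applies directly to the primary outcomes.

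**Conclusion.** The point holds. Seven co-equal primary outcomes, covering 17 endpoints in hypotheses 2-7, are tested at an unadjusted 0.05 with no success rule. With no effect and independent tests, the chance of at least one false positive is about 30% for seven and up to 58% for 17, or about 16% and 35% for false claims of benefit. Positive correlation reduces these by an amount the protocol does not allow one to fix. The figures also assume that each single test holds its nominal level, and count fruit and vegetables as one endpoint.

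The within-group clause is a defect on either reading, because it admits uncontrolled change or demands improvement in the control arm. This should be changed. It concerns what the protocol states, not detail left to an SAP.

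**What to change.** 1. In objectives 4-5 and hypotheses 2-9, delete the clause on change within the groups from baseline to six months. In section 3.17.3, label the paired t-tests and McNemar tests as descriptive.
2. State in section 3.17.3 that the group-by-time contrast in the GLMM already planned is the only test of effectiveness.
3. Apply Holm's procedure across the seven primary outcomes, so that the smallest p-value is compared with 0.05/7 = 0.0071, the next with 0.05/6 = 0.0083, and so on. Alternatively, name one primary outcome and make the other six secondary.
4. Represent dietary intake by one pre-specified score and treat the single foods as exploratory. The score must first settle where carbohydrates belong: hypothesis 7 expects them to fall, but section 3.16.6 puts them in neither its healthy nor its unhealthy list.

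The cost is wording in the protocol, carried into the SAP, with no added participants or measurements. The downside is a stricter threshold for individual outcomes, and hence less power for each.
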